
**Inclusion Criteria:**

**Inclusion criteria:** the sample from normotensive and hypertensive pregnant women in the third trimester, over 18 years old, and accepted at the IFF/Fiocruz to carry out prenatal care at the outpatient clinic and in the pregnant women's ward from July 2021 to September 2022. The minimum age of patients was defined according to the physiological differences observed between adolescent and adult pregnant women.

**Exclusion Criteria:**

**Exclusion criteria:** pregnant women with bleeding, with clear signs of premature birth (contraction, dilation), with pregnancy

twin, with fetal malformation, signs of eclampsia (based on blood tests, urine, and BP measurement), and HELLP syndrome.

**Risks:**

The risks of osteopathic treatment are small, especially with what we will do with pregnant women who are willing to participate in the search. The possible risk of feeling a little limp or a little dizzy. If she feels something different during the treatment, the pregnant woman must inform that we can decide whether or not to stop the treatment. Stopping therapy is usually enough to clear up any discomfort.

**Benefits:**

Osteopathic manipulative treatment (OMT) has been proven to help with painful processes in pregnant women. We are looking for a search aid in BP control in hypertensive pregnant women, which will be possible if the response to treatment is positive.

**Data Analysis Methodology:**

Relative risk (RR) and differences in means will be the measures of association used to assess the relationship between BMT and changes in hemodynamics as well as fetal outcomes. Categorical variables will be evaluated using the chi-frame test and numeric variables using the t-student test. The data will be digitized in the database with the help of Epi INFO and analyzed in SPSF

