**Study Design / Financial Support**

Study Design: Intervention/Experimental

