**Proposed Methodology:**

This is a cohort study with a convenience sample of normotensive and hypertensive pregnant women followed at the prenatal clinic and in the IFF/Fiocruz pregnant women's ward. The prenatal service at the IFF “takes care of pregnant women with a gestational age of less than 24 weeks, without clinical comorbidities and with indications such as infectious diseases with risk of fetal repercussion, adolescents aged Fifteen years, history of previous malformation pregnancies, maternal age 35 years or older, multiple gestations, hemolytic disease perinatal, and maternal gynecological malformation. "The services will take place at the Fernandes Figueira Institute, a unit of the Oswaldo Cruz Foundation dedicated to teaching, research, and technological development. The Institute is recognized as a reference center for the health of women, children, and adolescents. It has the “MS assignment of assisting, coordinating and evaluating actions aimed at women's and children's health within the scope of national." The research will be composed of two groups: a control group formed by normotensive pregnant women and an exposed group of pregnant women hypertensive. The appointments will take place on Tuesdays and Thursdays at the prenatal outpatient clinic or the pregnant women's ward of the IFF, with all pregnant women who agree to participate in the research. These will be met with OMT from their entry into the study until the time of termination of pregnancy. OMT consultations will occur at each routine visit of these pregnant women to the outpatient clinic. Pregnant women will respond to a standard form prepared by the researchers in addition to a life questionnaire, the SF-36, applied after each meeting. The average duration of consultations takes around 30 to 40 minutes, and the techniques chosen are widely recognized by osteopathic professionals and described in articles as safe practices. There will be no maneuvers on the patient's abdomen, just as there will be no maneuvers on the viscera, as it is not a practice of visceral osteopathy. Before and after each visit, the BP of the pregnant woman will be evaluated using a blood pressure device. OMRON HEM-7320F, validated for research by the Brazilian College of Cardiology1F. BP will always be measured on the left arm, with the patient sitting and in left lateral decubitus. Pregnant women who are hospitalized in the ward, they will also be treated with the same OMT but will have a different measurement. Before the OMT observes, the data of blood pressure (BP), heart rate (HR), and respiratory rate (RR) are present in the electronic monitor (without any interference by the human operator). An ultrasound (US) will be performed for fetal evaluation through the doppler of the uterine, umbilical and cerebral arteries, and then the same life questionnaire (QoL) will be applied. Only after these measurements will OMT occur. After 30 minutes of the intervention, the blood pressure, heart rate, and respiratory rate data on the electronic monitor will be measured again (without interference from the human operator). A new ultrasound will be performed for fetal evaluation through the doppler of the uterine, umbilical and cerebral arteries. One recent evaluation will be carried out 24 hours after OMT. Blood pressure, heart rate, and respiratory data will again be observed on the electronic display (without any interference by the human operator). Another ultrasound will be performed for fetal evaluation through the doppler of the uterine, umbilical and cerebral arteries, and then the same life questionnaire will be applied. The OMT protocol includes techniques for balance ligament (BLT), myofascial, muscular energy, and cranial tensions. High-velocity and low-speed (HVBA) styles were excluded. Pregnant women in both groups will maintain standard obstetric and drug treatment and must sign a free-term consent, their willingness, and awareness of participating in the research.

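### The plan attributes to OMT group contrasts that cannot show an OMT effect, because all women receive OMT and the groups are defined by hypertension status

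*Protocol*

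**What the plan says.** - **Analysis.** Data Analysis Methodology names relative risks and differences in means as the "measures of association used to assess the relationship between BMT and changes in hemodynamics as well as fetal outcomes", tested by chi-square and Student's t. It does not say whether the t-test is paired. The Introduction uses BMT for osteopathic manual treatment, so BMT and OMT are the same intervention.
- **Groups.** Proposed Methodology forms "a control group formed by normotensive pregnant women and an exposed group of pregnant women hypertensive". The sampling is described thus: "This is a cohort study with a convenience sample of normotensive and hypertensive pregnant women".
- **Treatment.** The OMT appointments are held "with all pregnant women who agree to participate in the research", and of these women it says: "These will be met with OMT from their entry into the study until the time of termination of pregnancy". Of women on the ward it says that "they will also be treated with the same OMT but will have a different measurement". No untreated, sham or delayed group is described. "Pregnant women in both groups will maintain standard obstetric and drug treatment".
- **Aims and outcomes.** Hypothesis and Primary Purpose concern the effect of OMT on hemodynamics and mean blood pressure. Secondary Purpose includes comparing the effects of OMT on vascularization between the groups. Secondary Outcome lists birth weight, gestational age at birth, resuscitation, NICU admission and death, controlled for start of prenatal follow-up, maternal age and weight gain.

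**The concern.** A relative risk for OMT needs some women with OMT and some without. Here OMT does not vary between the groups. What varies is hypertension status, together with whatever accompanies it in a non-randomised convenience sample: medication, comorbidity and care setting.

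The stake is misattribution. Under the section as worded, more NICU admissions or lower birth weight in hypertensive women could be reported as harm from OMT, and a larger fall in blood pressure in that group as benefit. The Benefits section looks to a positive response as support for OMT in blood pressure control, so the analysis statement bears directly on what the study will claim.

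**Working it through.** **The plan's own figure.** The only design number is a sample size of 80. The protocol gives no alpha, power, effect size, SD, event rate or group split, so 80 cannot be reproduced. The point does not depend on it.

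**Notation.** H is hypertensive, N is normotensive. Without OMT the mean blood pressures are μ_H and μ_N and the perinatal risks are p_H and p_N. OMT adds τ_H or τ_N to blood pressure and multiplies risk by k_H or k_N. Any change that would have occurred without OMT (rest, repeat measurement, regression to the mean, gestational trend) is d_H or d_N. Both groups are treated, so:

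- Difference in level = (μ_H − μ_N) + (τ_H − τ_N), taking d_H = d_N
- Difference in change = (τ_H − τ_N) + (d_H − d_N)
- Relative risk = (p_H × k_H) / (p_N × k_N)

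None of the three isolates τ or k. An effect common to both groups drops out of each.

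**Relative risk, assumed risks of 20% (H) and 10% (N).**

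| Effect of OMT on both groups | Risks | RR |
|---|---|---|
| none (k = 1) | 20% / 10% | 2.0 |
| halves (k = 0.5) | 10% / 5% | 2.0 |
| raises by half (k = 1.5) | 30% / 15% | 2.0 |

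If the effects differ, RR = 2.0 × k_H/k_N. With k_H = 0.5 and k_N = 1 it is 10%/10% = 1.0. Two groups with equal underlying risks and an inert OMT also give 1.0, so the figure cannot be traced back to OMT.

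**Blood pressure.** Simulation with assumed values: mean blood pressure 105 (H) and 85 (N) mmHg, between-woman SD 10, post-measurement noise SD 5, 40 women per group, 5,000 runs.

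| Common OMT effect (mmHg) | Difference in level | Difference in change |
|---|---|---|
| 0 | 19.98 | −0.03 |
| −5 | 20.00 | −0.02 |
| −10 | 20.03 | 0.01 |

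Neither contrast registers a common effect of up to 10 mmHg.

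**Chance of a significant result when OMT does nothing** (40 per group assumed, two-sided 0.05). For an existing blood pressure gap of 5, 10 or 20 mmHg with SD 10, the probability is 0.61, 0.99 and 1.00. For assumed risks of 25% and 10% it is 0.42.

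**Adjustment.** The three covariates under Secondary Outcome may reduce some differences between the groups. They cannot create variation in OMT.

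**The case against.** The strongest reply is that nothing in Data Analysis Methodology says the differences in means are between groups. Blood pressure is taken before and after each visit, and ward women are measured again 30 minutes and 24 hours after OMT. A paired pre/post difference would fit those data and the primary purpose, and paired versus unpaired testing is a detail an SAP commonly settles. Secondary Purpose also poses a legitimate between-group question, namely whether the vascular response differs.

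Much of this stands. A paired reading is open for the hemodynamic outcomes, and a comparison of response is a proper aim. It does not rescue the relative risks or the birth outcomes. These have no pre-OMT value, and no SAP can recover an OMT effect on them when everyone is treated. A paired change would also still be τ + d.

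A reader might infer more than the protocol supports:

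- *That the contrasts measure the effect of hypertension.* They do not do so cleanly. The sample is a convenience sample, background treatment continues, and the Introduction says hypertensive disorders usually come with other comorbidities. For blood pressure change, the target is a difference in response and not an effect of hypertension.
- *That the relative risk never moves with OMT.* This holds only for a common multiplier, as shown above.
- *That regression to the mean will produce an apparent benefit in hypertensive women.* That requires the classifying reading to serve also as baseline, which the protocol does not state. The Summary includes chronic hypertension, the Introduction bases diagnosis on an average of at least two measurements, and women may be on drug treatment at entry. It is a possibility whose size cannot be given from this document.

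**Conclusion.** The analysis statement is wrong as written. Between-group relative risks and mean differences in this design estimate a confounded association with hypertension status and cannot identify an OMT effect. For birth weight, gestational age, resuscitation, NICU admission and death, no contrast available in this design can do so. A between-group difference in blood pressure change shows at most whether the response differs by hypertension status. The within-woman change is the only quantity that carries information on OMT itself, and it is uncontrolled.

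This conclusion rests on the group definition and on OMT being given to all, both stated in the protocol. The risks, blood pressures, SDs and 40/40 split used above are assumptions. They illustrate the cancellation and do not predict results for this trial.

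**What to change.** Rewrite Data Analysis Methodology so that:

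1. The hemodynamic analysis of OMT is the within-woman pre-to-post change, tested as paired, reported separately in hypertensive and normotensive women, and described as uncontrolled.
2. The between-group difference in change is presented as a comparison of response by hypertension status.
3. Between-group relative risks and mean differences for perinatal outcomes are said to describe hypertensive versus normotensive women and not to be evidence for or against OMT.

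In Proposed Methodology, state that *exposed* and *control* refer to hypertension and not to OMT.

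The cost is wording only, with no new data. The downside is a weaker claim: the study would report short-term change under OMT without a comparator, and would make no statement about OMT and birth outcomes.

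It is tempting to add a rest period before the first session and subtract the rest change from the OMT change. This is not advised. If pressure settles by 5 mmHg during the rest and then levels off, and OMT does nothing, the subtraction gives 0 − (−5) = +5 mmHg, an apparent harm created by the fixed order.

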**Primary Outcome:**

The evolution of hemodynamic parameters during the third trimester of pregnancy

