**Study Details**

**Summary:**

The study seeks to evaluate the effects of osteopathic manipulative treatment (OMT) on the diaphragms in the hemodynamics of chronic and gestational hypertension in hypertensive pregnant women. OMT is already widely implemented as a therapy in normotensive pregnant women, including several RCTs proving its effectiveness in controlling musculoskeletal conditions. The search for OMT throughout pregnancy is a reality in countries like the USA and Australia. Australian observational studies (1,2) with pregnant women attest to the many women who seek and good results. In the USA, there was a reduction in complications during pregnancy and childbirth in a multicentric survey in osteopathic hospitals on pregnant women who had their prenatal care with OMT monitoring (3). Already in an ECR with a therapy-sacral skull, a specialty of osteopathy, a slight improvement in the pelvic pain of the pregnant women was observed (4). all studies do not report intercurrences or risks for pregnant women submitted to BMT throughout pregnancy. The present study, however, seeks to evaluate the possibility of improving perfusion with BMT in hypertensive pregnant women. As osteopathy is an integrative practice that does not use medication, positive research results could place it as an auxiliary therapy in controlling hypertension in hypertensive pregnant women.

The study provides a follow-up of the pregnant women who adhere to the research, from their acceptance until the end of the pregnancy. Therapy will be performed on the same days as the routine IFF prenatal consultations

References Requested

1- FRAWLEY, J. et al. Prevalence, and characteristics ofwomen who consult with osteopathic practitioners during pregnancy; a report from the Australian Longitudinal Study on Women’s Health (ALSWH).

Journal of Bodywork and Movement Therapies, v. 20, no. 1, p. 168–172, Jan. 2016.

2- SMITH, S. A study into osteopathic treatment of pregnant women in NSW and Queensland. PhD Thesis—[s.l.] Victoria University, 2005.

3-KING, H. H. et al. Osteopathic Manipulative Treatment in Prenatal Care: ARetrospective Case Control Design Study. P. 6, [n.d.].

4- ELDEN, H. et al. Effects of craniosacral therapy as adjunct to standard treatment for pelvic girl pain in pregnant women: a multicenter, single blind, randomized controlled trial. Acta obstetricia et gynecologica Scandinavica, v. 92, no. 7, p.775–782, 2013.

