**Primary Purpose:**

To evaluate the hemodynamic effects of OMT on the mean BP of pregnant women.

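### The third-trimester BP course ends at delivery; if BP affects when women deliver, plain means with t-tests make the late course in hypertensive women look too flat

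*Protocol*

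**What the plan says.** The Primary Outcome section gives "The evolution of hemodynamic parameters during the third trimester of pregnancy". It names no time point, no summary measure and no rule for a woman who delivers early. The Primary Purpose section is also general: "To evaluate the hemodynamic effects of OMT on the mean BP of pregnant women".

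Three statements fix when the data stop:
- Follow-up runs "from their acceptance until the end of the pregnancy" (Summary).
- On treatment: "These will be met with OMT from their entry into the study until the time of termination of pregnancy" (Proposed Methodology).
- In the clinic, readings are tied to treatment visits: "OMT consultations will occur at each routine visit of these pregnant women to the outpatient clinic", and "Before and after each visit, the BP of the pregnant woman will be evaluated using a blood pressure device" (Proposed Methodology). Ward patients are read from a monitor around the session and again a day later.

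The groups are "a control group formed by normotensive pregnant women and an exposed group of pregnant women hypertensive". Both receive the manipulation and both keep their usual obstetric care, so the study does not set the date of delivery. Gestational age at birth is a secondary outcome.

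The Data Analysis Methodology section names relative risk and differences in means as the measures, and then: "Categorical variables will be evaluated using the chi-frame test and numeric variables using the t-student test".

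**The concern.** Delivery ends treatment and measurement at the same moment, and its timing may not be independent of the outcome. If women with high or climbing BP deliver sooner, those still pregnant at 36, 38 or 40 weeks are increasingly selected for lower BP. A mean over whoever has a reading at a given week, or over all visits pooled, then understates the late rise. This would happen mainly in the hypertensive group and would narrow its gap to the normotensive group.

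The false flattening would resemble the BP control that the Benefits section hopes for. A t-test on means does nothing about it, and the outcome definition does not rule out the form of mean that suffers from it.

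**Working it through.** **Inputs from the protocol.** Readings end with pregnancy (Summary; Proposed Methodology). The outcome is a course over the third trimester (Primary Outcome). The analysis is differences in means with t-tests (Data Analysis Methodology). The total sample is 80, with no split, alpha, power or SD, so there is no planned figure to reproduce. The protocol gives no delivery rates and no link between BP and delivery, so everything numeric below is an assumption.

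**Check 1: delivery hazard rising with the last recorded BP.** Assumed for hypertensive women, with no treatment effect:
- mean BP 105 mmHg at week 28, between-woman SD 7, reading SD 5;
- mean rise 0.4 mmHg per week, slope SD 0.3 or 0.8;
- visits every 2 weeks from week 28 to week 40.

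From week 32 the chance of delivery per visit interval is h × exp(β × (last BP − 105)/10), with h = 0.05 or 0.12 and β = 0, 0.7 or 1.2.

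True rise, weeks 28 to 40: 12 × 0.4 = 4.8 mmHg. Bias is the mean in undelivered women minus the mean in all women. The observed rise is 4.8 plus the week-40 bias, up to rounding.

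| h | β | slope SD | undelivered at 40 wk | bias at 36 wk | bias at 38 wk | bias at 40 wk | observed rise 28–40 | first-to-last, all women |
|---|---|---|---|---|---|---|---|---|
| 0.05 | 0 | 0.3 / 0.8 | 81% / 82% | 0.0 | 0.0 | 0.0 | 4.8 | 4.4 |
| 0.05 | 0.7 | 0.3 | 74% | −0.5 | −0.8 | −1.2 | 3.6 | 4.6 |
| 0.05 | 0.7 | 0.8 | 73% | −0.8 | −1.4 | −2.3 | 2.5 | 4.4 |
| 0.05 | 1.2 | 0.3 | 65% | −1.3 | −2.0 | −2.6 | 2.2 | 5.0 |
| 0.05 | 1.2 | 0.8 | 63% | −1.9 | −3.2 | −4.7 | 0.0 | 4.5 |
| 0.12 | 0 | 0.3 / 0.8 | 60% / 60% | 0.0 | 0.0 | 0.0 | 4.8 | 4.0 |
| 0.12 | 0.7 | 0.3 | 49% | −1.4 | −2.1 | −2.8 | 2.0 | 4.5 |
| 0.12 | 0.7 | 0.8 | 48% | −2.0 | −3.4 | −5.0 | −0.2 | 4.0 |
| 0.12 | 1.2 | 0.3 | 40% | −2.8 | −3.9 | −4.9 | −0.2 | 4.9 |
| 0.12 | 1.2 | 0.8 | 41% | −3.9 | −5.9 | −8.0 | −3.2 | 4.1 |

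Three readings follow:
- With β = 0 there is no bias, however many women deliver early.
- With β above 0 the bias is always downward and grows with gestation.
- First-to-last change in all women is 4.0–5.0 mmHg. Its shortfall against 4.8 is also present at β = 0, where it reflects shorter follow-up and not selection on BP.

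**Check 2: delivery triggered by a threshold.** Assumed: entry at 28–33 weeks, entry BP 105 mmHg (SD 7), slope 0.5 mmHg per week (SD 0.6–0.9), reading SD 5, weekly readings, and a delivery probability of 0.5 at each reading at or above 118–126 mmHg from week 32. These thresholds are devices of the simulation, not clinical rules. Two runs on these assumptions gave:
- 4–22% delivered before 38 weeks, with the 38-week mean 0.7–3.2 mmHg too low against a true rise of about 3.75;
- 6–29% delivered before 38 weeks, with the 38-week mean 1.3–4.9 mmHg too low.

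Taken together, and rounded: about 5–30% delivered early and a bias of about 1–5 mmHg.

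**Check 3: does another analysis repair it?** In the harshest setting of check 1 (h = 0.12, β = 1.2, slope SD 0.8; 3,000 women), both models were fitted to the same observed readings:
- ordinary least squares on pooled visits: slope −0.251 per week × 12 = −3.0 mmHg;
- mixed model with random intercept and slope: 0.426 × 12 = +5.1 mmHg;
- truth: +4.8 mmHg.

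The mixed model works here because delivery depends on BP values that are in the data.

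**The case against.** The strongest reply is that the causal premise is not in the protocol. The Introduction says only that gestational hypertension raises the risk of pre-eclampsia and eclampsia. No section says that rising BP leads to earlier delivery, or that it does not do so in normotensive women. That stands: the bias is conditional, and its size comes from assumptions.

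Second, the analysis section does not say that means are taken over women still pregnant at each week. It speaks of changes in hemodynamics, and BP is taken before and after each session. A first-to-last change in all women would carry almost none of the flattering bias. A before-and-after difference within a visit, which was not simulated, should be affected much less. That also stands. But the protocol does not choose between these readings, so whether the primary result is biased rests on a choice it leaves open.

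Third, the size may be modest. If 40 per group, two-sided alpha 0.05 and 80% power are assumed, the detectable difference is 0.63 SD, or 0.63 × 7 = 4.4 mmHg at a between-woman SD of 7. Most of the 1–5 mmHg range lies below that, though its upper end does not.

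Fourth, handling of incomplete series often belongs in a statistical analysis plan, which is not at hand here. That is fair for detail. The protocol itself, however, fixes the t-test as the method for numeric variables.

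A reader might infer two stronger things. One is that the late course reflects only women whose BP stayed low. The simulations contradict this: with delivery dependent on BP, 40–74% of hypertensive women were still undelivered at week 40. The other is that the bias favours the trial's hypothesis. The Hypothesis section is non-directional, and only the Benefits section expresses a hope of BP control.

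**Conclusion.** The point holds in conditional form. The text establishes that readings end at delivery, that the primary outcome is a course over the third trimester, and that a comparison of means by t-test is the only numeric analysis stated. If BP influences the timing of delivery in the hypertensive group, means by gestational age or over pooled visits are biased downward late in pregnancy, mainly in that group. The size is about 1–5 mmHg at 38 weeks when 5–30% deliver before then, and more in harsher scenarios (up to 8.0 mmHg at week 40).

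The documents do not support saying that the bias is certain, or that its size is known. Nor do they support replacing the primary outcome with the change at the first session. That would answer an acute question in place of the protocol's third-trimester one. Without an untreated group it would also be open to settling and regression to the mean.

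The absence of an untreated comparator is a separate and larger limit. Even a course free of truncation bias could not be attributed to the treatment.

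**What to change.** Keep the third-trimester evolution as the primary outcome. In the Data Analysis Methodology section, replace the t-test on means for this outcome with a linear mixed model:
- all BP readings of all enrolled women;
- gestational age as the time scale;
- fixed effects for group, gestational age and their interaction;
- a woman-specific intercept and slope.

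Report gestational age at delivery by group; it is already collected. Add one form field for the reason for delivery and report that by group too. The listed data include the type of delivery but not its indication.

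The cost is a change of wording and one data field. The downside is that the result becomes model-based and relies on delivery depending on BP already recorded. If delivery follows a rise that no study reading captured, some bias remains. The change does not address the lack of an untreated group, and the report should say so.

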**Introduction**

Gestational hypertensive disorders (GHD) are a worldwide public health problem. They affect 6 to 8% of women and are the most common cause of pregnancy-related morbidity and mortality worldwide (1,2). GHD represents the main reason for fetal obituary and neonates with perinatal hypoxia (3,4). In Brazil, according to data from the 7th Brazilian guideline on arterial hypertension, the disease affects 7.5% of pregnancies and about 2% progress to eclampsia (5). The diagnosis of the hypertensive disease is given by the presence of high blood pressure. Systolic (SBP) at 140 mmHg and diastolic (DBP) at 90 mmHg, found in an average of at least two measurements in a period of 15 min (1–3). Gestational hypertensive disorders (GHD) are classified as pre-existing when the pregnant woman already presents a condition hypertensive before pregnancy; gestational hypertension (HG), when it appears during pregnancy and pre-eclampsia (PE). AS DHG usually is associated with other comorbidities such as diabetes, kidney disease, hematological disorders, liver, lung, and neurological pathology (2,3).HG manifests itself from the 20th week of gestation onwards and increases the risk of PE and eclampsia. The latter put the life of the fetus and the mother at risk as they are correlated with stroke and pulmonary edema (PE), which are the significant causes of mortality in this pathology. The HG approach involves changes in lifestyle and eating habits in addition to medication use. At the however, the use of medicines during the gestational period is complex since many of the drugs available go beyond the placental barrier and reach the bloodstream of the embryo, which, as it does not have a fully developed body system, is subject to adverse effects (6). Given this scenario, it is necessary to search for therapeutic alternatives for the treatment of DHG. In recent years, the increased demand for integrative and complementary practices (PIC) in the prevention and treatment of various diseases led the Organization World Health Organization (WHO) asks member states to formulate laws to integrate these practices into their health systems. THE Osteopathy is part of the list of PICs recognized in several countries, including Brazil. Osteopathic manual treatment (BMT) is configured as a non-invasive therapy without the use of drugs, where the professional diagnoses and treats somatic dysfunctions through the hands (6). The disorders treated by osteopathy are cataloged as diseases of the musculoskeletal system (ICD-10, M99.00-09) and identified by the TART parameters (Tenderness, Asymmetry, Range of motion change, Tissue texture change) (7). The importance of increasing research about OMT in pregnant women is due to the need to find safe and effective treatment practices during pregnancy, especially in high-risk pregnancies (8–10).

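### Entry is open across the third trimester but the stated analysis carries no gestational age, so the two groups' BP evolution and mean BP can refer to different weeks

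*Protocol*

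**What the plan says.** The Primary Outcome section names "The evolution of hemodynamic parameters during the third trimester of pregnancy". The Primary Purpose section speaks of mean BP and gives no time point.

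The Inclusion Criteria admit "the sample from normotensive and hypertensive pregnant women in the third trimester, over 18 years old". They name no entry week and no upper limit within the trimester.

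Proposed Methodology sets the period of treatment: "These will be met with OMT from their entry into the study until the time of termination of pregnancy". The Summary agrees, with follow-up running "from their acceptance until the end of the pregnancy". Readings follow the clinic calendar, not a grid of gestational weeks: "OMT consultations will occur at each routine visit of these pregnant women to the outpatient clinic", and "Before and after each visit, the BP of the pregnant woman will be evaluated using a blood pressure device". Women on the ward are measured on a different scheme around each treatment. The sample is one of convenience, with normotensive women as controls and hypertensive women as the exposed group; both receive osteopathic manipulative treatment (OMT).

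Data Analysis Methodology offers relative risks and differences in means, with "numeric variables using the t-student test". It contains no gestational-age term. The only covariates in the protocol stand under Secondary Outcome, for the birth outcomes: start of prenatal follow-up, maternal age and gestational weight gain. None of these is gestational age at study entry or at the reading.

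**The concern.** An outcome defined as evolution over a trimester needs a time axis. Here each woman contributes only the weeks from her own entry to her own delivery, and the stated comparison of means ignores which weeks those are. Two things can then enter the result without any woman's BP having changed because of treatment:

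- **Different weeks and lengths of follow-up.** If one group is observed later in pregnancy or for a shorter time, a contrast of mean BP or of first-to-last change contains part of the ordinary drift of BP with gestation.
- **Changing membership.** BP under OMT in the early third trimester can come only from early entrants. If later entrants have a different BP level, an average by week moves as they join.

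The groups have reason to differ in timing. A woman who becomes hypertensive or is admitted late in the trimester can join the hypertensive group only from then, whereas a normotensive clinic patient can join at its start. This problem arises at the start of follow-up and is separate from loss at delivery.

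**Working it through.** The protocol gives no figure on this point to reproduce: no entry distribution, visit weeks, BP drift or standard deviation. Every number below is an assumption used to show the range.

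**Assumed inputs.** Third trimester from week 28; entry uniform over the stated weeks; mean delivery week as stated; BP drift *s* = 0.3 to 1.0 mmHg per week, the same in both groups.

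**1. Coverage of early weeks.** If entry is uniform over weeks 28 to E, the share of eventual participants under observation at week w is (w − 28)/(E − 28), at most 1.

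| Entry window | Week 30 | Week 32 |
|---|---|---|
| 28–34 | 2/6 = 33% | 4/6 = 67% |
| 28–36 | 2/8 = 25% | 4/8 = 50% |
| 28–38 | 2/10 = 20% | 4/10 = 40% |

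**2. Shift in the contrast of mean BP.** A woman's mean observed week is (entry + delivery)/2. The shift is *s* × (hypertensive minus normotensive mean week).

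| Scenario | Hypertensive | Normotensive | Difference in weeks | Shift, mmHg |
|---|---|---|---|---|
| Same entry (28–36), same delivery (39) | 35.5 | 35.5 | 0 | 0 |
| Same entry (28–36), delivery 37 v 39 | 34.5 | 35.5 | −1.0 | −0.3 to −1.0 |
| Entry 32–36 v 28–32, delivery 39 in both | 36.5 | 34.5 | +2.0 | +0.6 to +2.0 |
| Entry 32–36 v 28–32, delivery 37 v 39 | 35.5 | 34.5 | +1.0 | +0.3 to +1.0 |
| Entry 28–32 v 32–36, delivery 39 in both | 34.5 | 36.5 | −2.0 | −0.6 to −2.0 |

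A simulation with a delivery SD of 1.2 weeks gave differences of 0, −0.99, +2.0, +1.02 and −2.0 weeks.

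**3. Extreme late-entry case.** Take normotensive entry over 28–30, hypertensive entry over 30–38, and all women followed to week 40.

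- Coverage of weeks 28–31, 32–35 and 36–39 is 75%, 100% and 100% in the normotensive group, against 6%, 50% and 94% in the hypertensive group.
- Mean observed weeks are (29 + 40)/2 = 34.5 and (34 + 40)/2 = 37.0. The difference is 2.5 weeks, a shift of 0.75 to 2.5 mmHg.
- If all readings are pooled, so that longer follow-up weighs more, the gap falls to about 2.1 weeks, or 0.6 to 2.1 mmHg.
- Mean follow-up is 40 − 29 = 11 weeks against 40 − 34 = 6. If evolution were taken as unscaled first-to-last change, the 5-week gap alone would separate the groups by 5 × *s* = 1.5 to 5 mmHg.

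**4. Changing membership.** With entry uniform over 28–36, women who enter at week 32 or later make up 0% of those observed at week 32 and (36 − 32)/(36 − 28) = 50% at week 36. If their BP level differs by 5 mmHg (assumed), the weekly average moves by 0.5 × 5 = 2.5 mmHg with no change in any woman. This can happen even when both groups enter alike.

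**The case against.** A reader might infer that the groups do refer to different weeks because hypertensive women enter late. The protocol does not support that:

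- It gives no entry timing by group. With identical entry and delivery patterns the shift in group means is zero.
- The Summary covers chronic as well as gestational hypertension, and chronically hypertensive women are eligible on the first day of the trimester.
- The Introduction says gestational hypertension "manifests itself from the 20th week of gestation onwards". That allows late onset but also onset before the third trimester.
- Proposed Methodology describes a service that takes women before 24 weeks, so early entry is feasible in either group, though not required.
- Earlier delivery among hypertensive women would pull the difference the other way. The 0.75 to 2.5 mmHg range is thus one extreme case, not an expected size.

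Three further objections carry weight. The groups are defined by BP, so a gap in level exists by construction, and a shift of 1 or 2 mmHg inside it is modest; for the same reason a type I error calculation that assumes equal group means would mislead. Readings before and after each visit are close in time, so within-visit change is largely untouched. And evolution could be read as within-woman change, with the model left to an SAP that is not shown.

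The last point does not dispose of the matter. The entry window and the time frame of the primary outcome belong in the protocol, and the protocol itself states a method that has no time axis. Medical records may hold earlier BP values (Details, under Other information), but nothing says that they feed the primary outcome, and values from before entry precede OMT.

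**Conclusion.** The point holds as a possibility that the design leaves open, not as a demonstrated bias. Open entry, observation only from entry, and a comparison of means without gestational age together allow the evolution and the mean level of BP to mix gestational week, length of follow-up and changing membership with change within women.

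Under the assumed patterns and drift, the contrast of mean BP shifts by zero to about 2 mmHg in either direction, and by up to 2.5 mmHg in the extreme late-entry case. All these figures rest on assumed entry windows, delivery weeks and slopes. The consequence falls mainly on the evolution outcome and on the size of the group contrast, not on within-visit change. The change should be made because it is cheap and because, without it, a trend cannot be separated from who was present in which week.

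**What to change.** In Primary Outcome and Data Analysis Methodology:

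- Use gestational age at each reading as the time axis, calculated from the date of last menstruation, which is already collected (Details, under Other information).
- Estimate evolution as within-woman change in a mixed model with group, gestational age, their interaction and gestational age at entry.
- Compare groups only over gestational weeks in which both have women under observation.

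This changes analysis wording and needs no new data. The cost is that the earliest weeks may drop out of the comparison if few women in one group are observed then. Because both groups receive OMT, the change aligns the groups by gestational week but does not turn their contrast into an estimate of the OMT effect.
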